## Abstract

**Background:**

Meta-analyses of telemonitoring for patients with heart failure conclude that it can lower the utilization of health services and improve health outcomes compared with the standard of care. A smartphone-based telemonitoring program is being implemented as part of the standard of care at a specialty care clinic for patients with heart failure in Toronto, Canada.

**Objective:**

The objectives of this study are to (1) evaluate the impact of the telemonitoring program on health service utilization, patient health outcomes, and their ability to self-care; (2) identify the contextual barriers and facilitators of implementation at the physician, clinic, and institutional level; (3) describe patient usage patterns to determine adherence and other behaviors in the telemonitoring program; and (4) evaluate the costs associated with implementation of the telemonitoring program from the perspective of the health care system (ie, public payer), hospital, and patient.

**Methods:**

The evaluation will use a mixed-methods approach. The quantitative component will include a pragmatic pre- and posttest study design for the impact and cost analyses, which will make use of clinical data and questionnaires administered to at least 108 patients at baseline and 6 months. Furthermore, outcome data will be collected at 1, 12, and 24 months to explore the longitudinal impact of the program. In addition, quantitative data related to implementation outcomes and patient usage patterns of the telemonitoring system will be reported. The qualitative component involves an embedded single case study design to identify the contextual factors that influenced the implementation. The implementation evaluation will be completed using semistructured interviews with clinicians, and other program staff at baseline, 4 months, and 12 months after the program start date. Interviews conducted with patients will be triangulated with usage data to explain usage patterns and adherence to the system.

**Results:**

The telemonitoring program was launched in August 2016 and patient enrollment is ongoing.

**Conclusions:**

The methods described provide an example for conducting comprehensive evaluations of telemonitoring programs. The combination of impact, implementation, and cost evaluations will inform the quality improvement of the existing program and will yield insights into the sustainability of smartphone-based telemonitoring programs for patients with heart failure within a specialty care setting.

## Introduction

### Background

Currently, one of the greatest challenges for health care systems worldwide is the growing fiscal and social burden of preventing and managing chronic diseases [1]. Heart failure (HF) is one of the most expensive chronic diseases, partly because 50% of patients with HF get readmitted within 1 year [2]. Evidence suggests approximately half of all readmissions are preventable and result from inadequate discharge teaching, nonadherence to medication, or failure to have early follow-up with a clinician [3].

There is mounting evidence that embedding self-care within existing health care services provides an effective model to meet these needs for a number of chronic diseases, including HF [4-7]. Although more traditional self-care interventions such as health coaching or patient education can be effective [8,9], their implementation often proves challenging [10,11]. Health information technology is one avenue that can support the delivery of self-care interventions. For example, telemonitoring (TM) is thought to be crucial to offer patients the right care at the right time [12] by allowing patients to collect clinical data at home, which is then transmitted via technology to be viewed and acted upon by a clinician at a distant location [13].

In HF, meta-analyses conclude that TM lowers the utilization of health services, improves HF health outcomes, and improves health-related quality of life (QoL) [14-20]. However, results vary widely between individual trials [21], and 2 of the largest studies, the Tele-HF [22] and BEAT-HF trials [23], reported null results. One problem is that results come from trials of varying quality, and there is often little discussion about the intervention itself or the degree to which the patients have adhered to it over the course of the study [24]. Furthermore, studies looking at the implementation of TM have identified technical, cost, organizational, and behavioral barriers, which may explain why these technologies are not yielding consistent positive outcomes [12,25]. In addition, this may explain why, despite some evidence of cost-effectiveness [26], there is still inconclusive evidence regarding the impact of TM in terms of its cost to patients with HF [26].

Although the ubiquity of mobile phones is believed to have the potential to make TM interventions more accessible and cost-effective [27,28], additional knowledge gaps exist in the emerging use of smartphones for TM of chronic diseases. Randomized controlled trials (RCTs) employing mobile phone–based TM interventions have been conducted and have shown similar positive results to those reported for more traditional TM [29,30]. However, this type of TM is novel, and therefore, there have been no comprehensive implementation studies on smartphone-based TM interventions completed to date.

### Implementation of a Smartphone-Based Telemonitoring Program

#### The Intervention

An algorithm-based smartphone-based TM program for patients with HF, called the Medly Program, is being implemented as part of the standard of care at the University Health Network’s Ted Rogers Center of Excellence for Heart Function in Toronto, Canada (hereafter referred to as the HF clinic). The objective of the Medly Program is similar to other HF TM programs: improve patient self-management and decrease health care utilization [31]. Patients enrolled in the Medly Program will receive a Medly kit that includes a smartphone (Samsung Galaxy Grand Prime) with a limited data plan and the Medly app already downloaded. In addition, patients receive a Bluetooth-enabled weight scale and blood pressure cuff. Patients are instructed to take daily weight and blood pressure readings using these devices and record their symptoms using the Medly app first thing in the morning. Automated self-care instructions are immediately displayed in the Medly app after these 3 parameters are processed by an algorithm that was developed in close consultation with HF clinicians. In addition, patients have access to graphs displaying historical trends for these parameters. To assist in compliance, patients receive an automated call on their primary phone line if they have not taken their readings before 10 AM. The Medly Program is initially providing patients with all the equipment to mitigate the potential operational and software development challenges of offering the service on different devices during the critical early stages of implementation. However, a transition to a *bring your own device* model is planned, which would enable patients with smartphones to use their own devices by downloading the Medly app.

If there are signs of deteriorating health of a patient, the Medly algorithm generates an alert to a HF clinician who is part of the patient’s care team. The alerts are made available to clinicians in 2 formats. The first is through an automated email containing the latest weight, blood pressure, and symptoms along with the patient’s target ranges. In addition, the email contains the patients’ latest medication list and HF–related laboratory results, and contact information. Second, clinicians can choose to view the alerts by accessing a secure Web portal that presents a list of all the alerts triggered. Here, clinicians can review details of the latest alert and graphs showing historical weight, blood pressure, symptoms, and HF–specific laboratory results, which are visually contextualized according to the patient’s target ranges. The clinician will follow-up with the patient depending on the clinical need, documenting all actions and decisions taken in response to the alert in the hospital electronic medical record (EMR).

The Medly Program is intended to be delivered as part of the standard of care; as such, the goal is for it to be seamlessly integrated within the existing workflows of the HF clinic. Before deployment, a service blueprint was created through ethnographic methods including observation and informal interviews with clinicians and support staff in the HF clinic. This helped identify areas where the processes of the Medly Program could be incorporated. In addition, an RCT of 100 patients with an embedded qualitative component was previously conducted in the HF clinic with an earlier version of the Medly system. This study concluded that patients receiving the intervention experienced improvements in QoL and self-care maintenance compared with a control group [30]. Lessons learned from this RCT helped justify the decision to implement the Medly Program as part of the standard of care and informed the program’s implementation strategy. The current program offers an opportunity to evaluate the implementation and effectiveness of Medly under real-world conditions.

#### User Training and Support

Training as to how to use the Medly app and associated devices is provided to patients at the time of enrollment into the Medly Program by a telehealth analyst. Clinicians monitoring patients through the Medly system participated in a formal training session approximately 1 month before program deployment. Both patients and clinicians are provided with a user manual to supplement the in-person training along with contact information of the telehealth analyst who offers technical support during normal business hours.

### Evaluation Objectives and Research Questions

#### Objective 1

The first objective is to evaluate the impact of the Medly Program on health service utilization, patient health outcomes, and their ability to self-care. Alerts sent to patients and clinicians will help identify periods of symptom exacerbation and volume overload. The impact of this is expected to permit earlier intervention for worsening conditions, thus avoiding trips to the emergency department (ED) and hospitalizations. For patients who are enrolled into the Medly Program on hospital discharge, the program is expected to reduce 30-day readmission rates. In addition, participation in the Medly Program is expected to improve patients’ ability to self-care, leading to improved clinical outcomes and QoL.

#### Objective 2

The second objective is to evaluate the degree to which the Medly Program was implemented as intended and to identify the contextual barriers and facilitators of implementation. This objective will answer the following questions:

To what extent did the HF clinic implement the Medly Program as intended?What contextual factors influence the implementation of the Medly Program?What adaptations were needed to implement and sustain the program within existing clinical workflows?

#### Objective 3

The third objective is to describe patient usage patterns to determine adherence and other behaviors in the Medly Program. This objective will answer the following questions:

To what degree do patients adhere to the Medly Program and how do adherence patterns change over time?What factors influence patient adherence?

#### Objective 4

The fourth objective is to evaluate the costs associated with the implementation of the TM program from the perspective of the health care system (ie, public payer), the hospital, and patients.

## Methods

### Overview of the Study Design and Evaluation Framework

Data for the 4 objectives will be collected using mixed-methods. This approach will include a multiple pre-and posttest design for the evaluation of patient-level impacts, patient adherence, and cost. Quantitative data will include data collected as part of the standard of care (including health care utilization data and laboratory results obtained using a chart review) and usage data from the TM system. Additional patient-level data will be collected using questionnaires at baseline, 1 month, 6 months, 12 months, and 24 months. The qualitative component will take the form of an embedded single case study [32]. The 2 embedded subunits of analysis include clinicians and patients, as it relates to their adoption and use of the Medly system. The case is defined as the Medly Program at the HF clinic for the duration of 1 year starting from the program’s launch date (August 23, 2016). Qualitative methods, including semistructured interviews and document reviews, will be used to gain insights regarding patient self-care practices (objective 1), the barriers and facilitators to program implementation (objective 2), and explanations for patient adherence and usage of the system (objective 3).

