### Data Collection and Analysis

#### Objective 1: Measuring the Impact of the Medly Program

##### Impact Indicators

The primary outcome for evaluating the impact of the Medly Program is the number of hospitalizations because of HF in the 6 months before versus the 6 months after enrollment. Secondary impact outcomes comparing 6-month to baseline values are described below.

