##### Data Acquisition

Data collection will occur at baseline, 1 month, 6 months, 12 months, and 24 months, or until the patient exits the program. Data collected in addition to the primary evaluation period (baseline to 6 months) will provide an opportunity for post-hoc analyses aimed at quality improvement, including recommended duration of use. For example, the 1-month time point was included to determine if the bulk of changes to self-care and QoL occur immediately after enrollment. Similarly, longitudinal data will help determine whether patient-level impacts are sustained or change when using the system long term.

Health service utilization, laboratory results, mortality, prediction of survival, and select demographic information will be obtained from the hospital EMR. In addition, health service utilization information will be verified by patient participants through self-reports via a questionnaire.

Baseline and follow-up questionnaires containing the validated survey tools listed in Table 1 will be distributed to patients during regularly scheduled visits. Upon study enrollment, patients will be asked whether they prefer to be mailed the questionnaire or completing it using an online survey tool (SurveyMonkey [38]) in the event that they do not have a clinic visit scheduled for the data collection time point. In these situations, the questionnaires will be sent to the patient according to the preferred format and they will be given 2 weeks to respond, after which a member of the evaluation team will call the patient to remind them to complete the questionnaire.

**Table 1 table1:** Timing of outcome assessments for the impact evaluation.

Domain and measure		Baseline	1 month	6 months	12 months	24 months	Exit

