**Health service utilization**							
	30-day readmission		X^a^				
	Number of hospitalizations	X		X	X	X	X
	Number of days in hospital	X		X	X	X	X
	Number of emergency department visits	X		X	X	X	X
	Number of heart failure-related outpatient visits	X		X	X	X	X
	Number of visits to family doctors	X		X	X	X	X
	Changes to medication	X		X	X	X	X

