##### Data Acquisition

Costs will be calculated using a 6-month time frame. Specifically, we will compare costs before the implementation of the Medly Program (assessed at baseline) versus the costs after enrollment of patients into the program (measured at 6 months). This time frame was chosen because it represents the time horizon over which most of the health effects and costs of using the Medly Program are expected. Most of the cost variables will be self-reported by patients and triangulated using administrative data whenever possible (eg, EMR data). Therefore, questions related to the cost will be added to the patient outcome questionnaires (objective 1) and will be administered at baseline and 6 months.

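### The design is labelled multiple pretest, but no outcome has more than one pre-enrollment value, so the single 6-month before window cannot be checked for regression to the mean

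*Protocol article*

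**What the plan says.** All places are in the protocol article.

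- **Design label.** The overview of the study design calls it "a multiple pre-and posttest design for the evaluation of patient-level impacts, patient adherence, and cost". The abstract says "a pragmatic pre- and posttest study design for the impact and cost analyses", without the word multiple and without adherence.
- **Primary outcome.** Impact Indicators defines it as "the number of hospitalizations because of HF in the 6 months before versus the 6 months after enrollment", which is one window on each side.
- **Schedule.** Objective 1, Data Acquisition: "Data collection will occur at baseline, 1 month, 6 months, 12 months, and 24 months, or until the patient exits the program". Table 1 has one pre-enrollment column, baseline, and several later ones. 30-day readmission has no baseline mark, and Planned Analyses compares it with a clinic rate from before launch. Mortality is tracked forward against a model projection.
- **Primary tests.** Planned Analyses (Objective 1) specifies paired t and Wilcoxon signed rank tests of baseline against 6 months.
- **Cost.** Objective 4 compares one before value with one after value. The cost questions "will be administered at baseline and 6 months".
- **Adherence.** It is the share of days with a complete Medly reading, so it exists only after enrollment.
- **Source.** Utilization comes from the hospital EMR and is verified by patient questionnaire.
- **Context.** The research objectives and Planned Analyses both refer to patients enrolled at hospital discharge. Limitations accepts that there is no distinct comparator group.

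**The concern.** With no comparator, each patient's own past is the only control for the primary outcome. Several pretests are what would show whether that past is represented fairly. A reader of the design overview would credit the study with this protection, and the schedule does not provide it.

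The gap is relevant in this population. A patient enrolled at discharge after an HF admission has, by construction, at least one event at the end of the before window. Admissions would then tend to fall afterwards even if the program did nothing. With one window before and one after, a fall of that kind looks the same as a program effect.

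**Working it through.** **1. What the sample size assumes.** Inputs from Power Consideration: d = 0.3, 80% power, two-sided alpha 0.05, 20% loss, target 108.
- Normal approximation for a paired difference: ((1.960 + 0.842)/0.3)² = 87.2, so 88 pairs, and 88/0.8 = 110.
- Noncentral t: 90 pairs, and 90 × 1.2 = 108.

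The stated 108 is therefore reproduced, exactly or within 2 patients, by a comparison of one pre value with one post value. The sample size agrees with the operative text and not with the label. Completers: 108 × 0.8 = 86.4, taken as 86.

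**2. Pre-enrollment values by outcome.**

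| Outcome | Patient-level values before enrollment |
|---|---|
| HF hospitalizations (primary) and other utilization counts | 1 |
| Laboratory, LVEF, dyspnea, quality of life, self-care | 1 |
| Cost | 1 |
| 30-day readmission, mortality | 0 |
| Adherence | 0 (cannot exist) |

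No row has more than one.

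**3. Effect of an atypical last window when the program has no effect.** The documents give no admission rate, dispersion or correlation, so these are assumptions: patient rates follow a gamma distribution with shape 1 and mean μ per 6 months, counts are Poisson, the last pre-window runs at m times the usual rate, and the post window returns to the usual rate. For the difference D = before − after:
- E(D) = μ(m − 1)
- Var(D) = μ(m + 1) + μ²(m − 1)²

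With μ = 0.5 and m = 1.5, E(D) = 0.25 and Var(D) = 1.25 + 0.0625 = 1.3125. The spurious standardized effect is 0.25/√1.3125 = 0.218, against the planned 0.3. With 86 pairs, z = 0.218 × √86 = 2.02, and the chance of significance is about Φ(2.02 − 1.96) ≈ 52%. Simulation of the paired t test agrees (52 to 53%).

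Same formula, other values:

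| μ | m | E(D) | Var(D) | z, 86 pairs | Chance of a significant fall |
|---|---|---|---|---|---|
| 0.5 | 1.2 | 0.10 | 1.110 | 0.88 | 14% |
| 0.5 | 1.5 | 0.25 | 1.3125 | 2.02 | 52% |
| 0.33 | 1.5 | 0.167 | 0.861 | 1.67 | 38% |
| 0.8 | 1.5 | 0.40 | 2.160 | 2.52 | 71% |

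To put m = 1.5 in context: if a share q of patients brings one extra index admission into the window, the before mean is 0.5 + q, and 0.75 is reached at q = 0.25. The share enrolled at discharge is not given.

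**4. With earlier windows.** If the two earlier windows run at the usual rate, the contrast of post with their mean has expectation zero, and a paired t test rejects about 5% of the time. Averaging the last window in with them removes only part of the bias. The mean of all three pre-windows is (1.5 + 1 + 1)/3 = 1.167 times usual, so E(D) = 0.083, Var(D) = 0.5 × (1 + 3.5/9) + 0.25 × 0.167² = 0.701, z = 0.92, and rejection is about 15%. The last window therefore needs its own term.

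**The case against.** **The label is harmless.** Multiple can be read as repeated follow-up or as several outcomes. The primary definition, Table 1, the tests, the cost comparison and the sample size all agree on one pre and one post value, so nobody would run a different analysis because of the phrase. This largely stands: correcting the label alone is clerical. It does not rescue adherence, which has no pretest on any reading.

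**The limitation is already disclosed.** Limitations admits the missing comparator and offers detailed description and comparison with other trials. One window on each side is a legitimate pragmatic choice. This stands too, but description cannot show whether the before window was typical.

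**Enrollment has passed the target.** With 166 enrolled, about 166 × 0.8 = 132 would complete. That improves precision but not bias: in the 1.5-fold scenario z rises to 0.218 × √132 = 2.51, and the chance of a spurious result to about 71%.

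**A tempting stronger reading: more pretests would raise power.** The documents do not support it. It requires a stable pre-enrollment rate. With 86 pairs, mean 0.5 and a true 50% reduction, a paired t test on post minus the mean of 1, 2 or 3 pre-windows has power of about 74/87/92% if the rate is stable. If earlier rates are 20% lower, it is 75/75/74%; if 50% lower, 74/41/27%. Discharge enrollment makes lower earlier rates plausible. Nor would the primary test gain, since its contrast is unchanged.

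**Earlier data are weaker.** They would lack the patient self-report check and may be incomplete for patients not yet known to the hospital. This stands, and it is why they can only be supportive.

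**Conclusion.** Two things hold. The design overview misdescribes the study: at most one pretest exists for any outcome, and none for adherence, 30-day readmission or mortality at patient level. And, with no comparator and some enrollment at discharge, the planned before-after contrast cannot tell a program effect from regression to the mean, although the EMR already in use may supply earlier windows that would help check this.

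The size is conditional. With a usual mean of 0.5 admissions, the chance of a spurious significant fall is about 14% if the last window is 1.2 times usual and 52% if it is 1.5 times. At 1.5 times it ranges from 38% to 71% for means of 0.33 to 0.8. All these rates are assumed. A reader might infer that the primary result will be a false positive. The documents do not support that, because they give neither the admission rate nor the share enrolled at discharge. What follows is that the plan as described has no check on this bias.

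The check also has limits. If HF was truly worsening before enrollment, earlier windows would understate what to expect without the program. This is a low-cost improvement and does not invalidate the primary analysis.

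**What to change.** 1. Keep the Impact Indicators contrast (6 months before against 6 months after) as primary, with its tests and sample size.
2. For hospitalizations, hospital days and ED visits taken from the EMR, also extract months -18 to -12 and -12 to -6 before enrollment, and display counts and observed person-time by window.
3. Prespecify one supportive count model for repeated counts within patient: log E(count) = log(observed person-time) + intercept + b1 × (last pre-window) + b2 × (post-enrollment). The reference is the two earlier windows. exp(b1) shows whether the last window was atypical, and exp(b2) contrasts post-enrollment with the earlier windows. Read it as a check on regression to the mean, and claim no power gain.
4. Reword the design overview: a single pretest with multiple posttests for impact, pre-post for cost, and post-enrollment measurement only for adherence. State that 30-day readmission is compared with a historical clinic rate.

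**Cost.** More chart extraction from the same EMR for the same patients, one extra model, and a wording change, with no new visits or questionnaires. The article expects the primary impact analysis by January 2019, so at the time of writing this could still be specified beforehand. Person-time handles periods without records but not admissions elsewhere that the EMR missed, so the earlier windows remain supportive.
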